### **3. Work-related Physical Activity**

3.1 In the past week, did you work for pay or as a volunteer?

(1) no (end); (2) yes

3.1.a How much time do you work for pay or as a volunteer for a week: \_\_\_\_\_ hours

3.1.b Which of the following descriptions best presents your work for pay or as a volunteer

(1) frequent sitting, light upper extremity activity (e.g., office work, ticket takers, etc.)

(2) sitting or standing often, with only a small amount of walking (e.g., cashiers, etc.)

---

(3) often running, need to carry general heavy objects (such as waiters, letter carriers, etc.)

(4) frequent running, need to carry quite heavy objects (such as construction workers)

---

## **Leisure-time Activity Preferences**

1.1 Do you like walking outside the home?

(1) strongly dislike; (2) dislike somewhat; (3) neutral; (4) like somewhat; (5) strongly like

1.2 Do you like light-intensity sports?

(1) strongly dislike; (2) dislike somewhat; (3) neutral; (4) like somewhat; (5) strongly like

1.4 Do you like vigorous-intensity sport?

(1) strongly dislike; (2) dislike somewhat; (3) neutral; (4) like somewhat; (5) strongly like

1.5 Do you like muscle strength exercises?

(1) strongly dislike; (2) dislike somewhat; (3) neutral; (4) like somewhat; (5) strongly like

---

## **Sedentary Behavior Measurement Form**

1.1 In the past week, how much time in total did you spend sitting and doing the following intellectual activities during your free time?

1.1.a Play chess (including Chinese chess, go, checkers, etc.) \_\_\_\_\_ hours \_\_\_\_\_ minutes

1.1.b Play tiles (mahjong, poker, and solitaire) \_\_\_\_\_ hours \_\_\_\_\_ minutes

1.1.c Calligraphy, painting, reading, and writing \_\_\_\_\_ hours \_\_\_\_\_ minutes

1.2 In the past week, how much time in total did you spend sitting in your free time (including watching TV, riding in the car, talking, needlework, etc.) \_\_\_\_\_ hours \_\_\_\_\_ minutes

---

### Self-Efficacy for Exercise Scale

How confident are you right now that you could exercise three times per week for 20 minutes if:

| Item                                          | Not Confident |   |   |   |   |   |   |   |   |   | Very Confident |  |  |  |  |  |  |  |  |  |
|-----------------------------------------------|---------------|---|---|---|---|---|---|---|---|---|----------------|--|--|--|--|--|--|--|--|--|
| 1.1 the weather was bothering you             | 0             | 1 | 2 | 3 | 4 | 5 | 6 | 7 | 8 | 9 | 10             |  |  |  |  |  |  |  |  |  |
| 1.2 you were bored by the program or activity | 0             | 1 | 2 | 3 | 4 | 5 | 6 | 7 | 8 | 9 | 10             |  |  |  |  |  |  |  |  |  |
| 1.3 you felt pain when exercising             | 0             | 1 | 2 | 3 | 4 | 5 | 6 | 7 | 8 | 9 | 10             |  |  |  |  |  |  |  |  |  |
| 1.4 you had to exercise alone                 | 0             | 1 | 2 | 3 | 4 | 5 | 6 | 7 | 8 | 9 | 10             |  |  |  |  |  |  |  |  |  |
| 1.5 you did not enjoy it                      | 0             | 1 | 2 | 3 | 4 | 5 | 6 | 7 | 8 | 9 | 10             |  |  |  |  |  |  |  |  |  |
| 1.6 you were too busy with other activities   | 0             | 1 | 2 | 3 | 4 | 5 | 6 | 7 | 8 | 9 | 10             |  |  |  |  |  |  |  |  |  |
| 1.7 you felt tired                            | 0             | 1 | 2 | 3 | 4 | 5 | 6 | 7 | 8 | 9 | 10             |  |  |  |  |  |  |  |  |  |
| 1.8 you felt stressed                         | 0             | 1 | 2 | 3 | 4 | 5 | 6 | 7 | 8 | 9 | 10             |  |  |  |  |  |  |  |  |  |
| 1.9 you felt depressed                        | 0             | 1 | 2 | 3 | 4 | 5 | 6 | 7 | 8 | 9 | 10             |  |  |  |  |  |  |  |  |  |

---

## Physical Activity Self-Regulation Scale

Please comment on the following questions according to your actual situation.

| Items                                                                | Never | Rarely | Sometimes | Often | Very often |
|----------------------------------------------------------------------|-------|--------|-----------|-------|------------|
| 1.1 I mentally kept track of my PA                                   | 1     | 2      | 3         | 4     | 5          |
| 1.2 I mentally noted specific things that helped me be active        | 1     | 2      | 3         | 4     | 5          |
| 1.3 I set short term goals for PA                                    | 1     | 2      | 3         | 4     | 5          |
| 1.4 I asked someone for PA advice or demo                            | 1     | 2      | 3         | 4     | 5          |
| 1.5 I asked a PA expert or health professional for PA advice or demo | 1     | 2      | 3         | 4     | 5          |
| 1.6 I reminded myself of PA health benefits                          | 1     | 2      | 3         | 4     | 5          |
| 1.7 I mentally scheduled specific times for PA                       | 1     | 2      | 3         | 4     | 5          |
| 1.8 I rearranged my schedule to ensure I had time for PA             | 1     | 2      | 3         | 4     | 5          |
| 1.9 I purposely planned ways to do PA when on trips away from home   | 1     | 2      | 3         | 4     | 5          |
| 1.10 I purposely planned ways to do PA in bad weather                | 1     | 2      | 3         | 4     | 5          |

Abbreviations: PA, physical activity; demo, demonstration.

---

## Telephone Interview for Cognitive Status

Now I will ask you a few questions, some of which may be easy for you and some of which may be difficult.

1.1 What is today's year/month/date?

year (1) correct; (2) incorrect

month (1) correct; (2) incorrect

date (1) correct; (2) incorrect

1.2 What is the day of the week? (1) correct; (2) incorrect

1.3 What season are we in? (1) correct; (2) incorrect

1.4 How do you feel about your memory now?

(1) excellent; (2) very good; (3) good; (4) average; (5) bad

1.5 I'm going to read you a list of ten words. Please listen carefully and try to remember them. When I am done, tell me as many words as you can, in any order. Ready?

The words are: hat, car, tree, elephant, cinema, watch, pillow, hospital, pencil, table tennis.

Now tell me all the words you can remember. Answered correctly \_\_\_\_\_ words.

1.6 We will ask you some subtractions.

(1) One hundred minus 7 equals what? \_\_\_\_\_

(2) And 7 from that (the answer to (1))? \_\_\_\_\_

(3) And 7 from that (the answer to (2))? \_\_\_\_\_

(4) And 7 from that (the answer to (3))? \_\_\_\_\_

(5) And 7 from that (the answer to (4))? \_\_\_\_\_

---

The number of answers correctly \_\_\_\_\_

1.7 The ten words I read to you earlier, please tell me the words you remember now.

Answered correctly \_\_\_\_\_ words.

## Pittsburgh Sleep Quality Index

|     | Items                                                                                                                                                                         | Options                   |                       |                      |                            |
|-----|-------------------------------------------------------------------------------------------------------------------------------------------------------------------------------|---------------------------|-----------------------|----------------------|----------------------------|
|     |                                                                                                                                                                               | (1)                       | (2)                   | (3)                  | (4)                        |
| 1.1 | During the past month, what time have you usually gone to bed at night? Bedtime _____                                                                                         |                           |                       |                      |                            |
| 1.2 | During the past month, how long (in minutes) has it usually taken you to fall asleep each night? Number of minutes _____                                                      | $\leq 15$ min             | 16~30 min             | 31~60 min            | $> 60$ min                 |
| 1.3 | During the past month, what time have you usually gotten up in the morning? Getting up time _____                                                                             |                           |                       |                      |                            |
| 1.4 | During the past month, how many hours of actual sleep did you get at night? (This may be different than the number of hours you spent in bed.) Hours of sleep per night _____ |                           |                       |                      |                            |
| 1.5 | During the past month, how often you had trouble sleeping because you...                                                                                                      |                           |                       |                      |                            |
|     | a. Cannot get to sleep within 30 minutes                                                                                                                                      | not during the past month | less than once a week | once or twice a week | three or more times a week |
|     | b. Wake up in the middle of the night or early morning                                                                                                                        | not during the past month | less than once a week | once or twice a week | three or more times a week |
|     | c. Have to get up to use the bathroom                                                                                                                                         | not during the past month | less than once a week | once or twice a week | three or more times a week |

|     |                                                                                                                           |                           |                       |                      |                            |
|-----|---------------------------------------------------------------------------------------------------------------------------|---------------------------|-----------------------|----------------------|----------------------------|
|     | d. Cannot breathe comfortably                                                                                             | not during the past month | less than once a week | once or twice a week | three or more times a week |
|     | e. Cough or smore loudly                                                                                                  | not during the past month | less than once a week | once or twice a week | three or more times a week |
|     | f. Feel too cold                                                                                                          | not during the past month | less than once a week | once or twice a week | three or more times a week |
|     | g. Feel too hot                                                                                                           | not during the past month | less than once a week | once or twice a week | three or more times a week |
|     | h. Had bad dreams                                                                                                         | not during the past month | less than once a week | once or twice a week | three or more times a week |
|     | i. Have pain                                                                                                              | not during the past month | less than once a week | once or twice a week | three or more times a week |
|     | j. Other reason(s), please describe _____. How often during the past month have you had trouble sleeping because of this? | not during the past month | less than once a week | once or twice a week | three or more times a week |
| 1.6 | During the past month, how would you rate your sleep quality overall?                                                     | very good                 | fairly good           | fairly bad           | very bad                   |
| 1.7 | During the past month, how often have you taken medicine to                                                               | not during the past month | less than once a week | once or twice a week | three or more times a week |

---

|     |                                                                                                                                  |                           |                            |                       |                            |
|-----|----------------------------------------------------------------------------------------------------------------------------------|---------------------------|----------------------------|-----------------------|----------------------------|
|     | help you sleep (prescribed or “over the counter”)?                                                                               |                           |                            |                       |                            |
| 1.8 | During the past month, how often have you had trouble staying awake while driving, eating meals, or engaging in social activity? | not during the past month | less than once a week      | once or twice a week  | three or more times a week |
| 1.9 | During the past month, how much of a problem has it been for you to keep up enough enthusiasm to get things done?                | no problem at all         | only a very slight problem | somewhat of a problem | a very big problem         |

## Adverse Event Log

| Participants'
ID number | Date Reported
(mm/dd/yyyy) | Adverse
Event | Start
Date/Time
(mm/dd/yyyy
2400 clock) | Outcome
1=Resolved
2= Resolved
w/sequelae
3=Recovering
4=Unknown
5=Fatal | End Date/Time
(mm/dd/yyyy
2400 clock) | Severity
1= mild
2= mod
3= severe | Action Taken
as a result of
Adverse Event
0= None
1= Refer to
Primary Care
Physician
2= Other; please
explain | Withdrawal
Did subject
withdraw
from the study
as a result of
this AE?

Yes/No | Is
Adverse
Event
serious?
(Determin
ed by the
Physician)

Yes/No | Related to
Intervention
(Completed
by the
Physician)

1=Definitely
2=Probably
3=Possibly
4=Unrelated
5=Unknown | Serious of
Adverse Event
(Determined by
the Physician)

Yes/No | Unexpected
Adverse Event
(Completed by
the Physician)

Was the AE
unexpected in
nature,
severity, or
frequency?

Yes/No |
|----------------------------|-------------------------------|------------------|--------------------------------------------------|--------------------------------------------------------------------------------------------|---------------------------------------------|--------------------------------------------|---------------------------------------------------------------------------------------------------------------------------------------|-----------------------------------------------------------------------------------------------------|------------------------------------------------------------------------------------------|----------------------------------------------------------------------------------------------------------------------------------------------|-------------------------------------------------------------------------------|----------------------------------------------------------------------------------------------------------------------------------------------------------|
|                            |                               |                  |                                                  |                                                                                            |                                             |                                            |                                                                                                                                       |                                                                                                     |                                                                                          |                                                                                                                                              |                                                                               |                                                                                                                                                          |
|                            |                               |                  |                                                  |                                                                                            |                                             |                                            |                                                                                                                                       |                                                                                                     |                                                                                          |                                                                                                                                              |                                                                               |                                                                                                                                                          |
|                            |                               |                  |                                                  |                                                                                            |                                             |                                            |                                                                                                                                       |                                                                                                     |                                                                                          |                                                                                                                                              |                                                                               |                                                                                                                                                          |
|                            |                               |                  |                                                  |                                                                                            |                                             |                                            |                                                                                                                                       |                                                                                                     |                                                                                          |                                                                                                                                              |                                                                               |                                                                                                                                                          |
|                            |                               |                  |                                                  |                                                                                            |                                             |                                            |                                                                                                                                       |                                                                                                     |                                                                                          |                                                                                                                                              |                                                                               |                                                                                                                                                          |

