### Adverse Events

---

A surveillance form will be used to screen for adverse events (AEs) and serious adverse events at each assessment visit (see Appendix A). Serious, unexpected AEs that are related or are possibly related to the study will be reported to the Institutional Review Board (IRB) immediately.

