## **Data Analysis Plan**

### **1. Primary Analyses**

The primary aim will be to assess the leisure-time activity level at 8 weeks in the context of linear mixed model effects multilevel models. In this analysis, the intention-to-treat approach will be used. In addition to the intervention group, assessment time, and their interaction terms, the model may include individual-level (age, sex) variables as explanatory covariates. A random village intercept term is included to account for clustering by villages. The primary study hypothesis of SAWA will be tested based on a two-tailed significance level of 0.05.

An intention-to-treat analysis that includes all randomized participants, regardless of the number of assessments obtained, will be conducted. The analytical plans are flexible and will be adapted as scientific perspectives are advanced.

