### **2. Secondary Analyses**

#### **a. Handling of missing data**

Although substantial effort will be employed to minimize missing data, it is inevitable that some missing data will occur. Missing data are expected due to drop outs and missed visits. The leisure-time activity level is a subject-level variable and missing assessments would influence tests relative to treatment-by-time interactions. The primary analysis described above will be conducted within each dataset using linear mixed effect models and employ restricted maximum likelihood using all available data. Results of datasets will be combined to produce final estimates for between-group comparisons. This approach assumes data are missing at random: the mechanism that gives rise to missing data relies on observed data only. To assess the sensitivity and robustness of the results, we will compare results of two sets of analyses: i) all participants, with or without missing data, were subjected to the repeated measures linear mixed model analysis; ii) we will perform the linear mixed model with missing

---

data imputed using multiple imputation.

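### The adverse event log has no outcome code for an unresolved event that is stable or worsening, so such events cannot be coded truthfully

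*Supplement*

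**What the plan says.** Under Data Collection, Adverse Events, the final protocol states: "A surveillance form will be used to screen for adverse events (AEs) and serious adverse events at each assessment visit". The form is the Adverse Event Log in Appendix A. Four of its columns matter here.

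- Outcome, a closed list: "1=Resolved 2= Resolved w/sequelae 3=Recovering 4=Unknown 5=Fatal".
- End date, a date and time field: "End Date/Time (mm/dd/yyyy 2400 clock". No instruction says what an empty field means.
- Action taken: none, referral to a primary care physician, or "2= Other; please explain".
- Participation, answered yes or no: "Withdrawal Did subject withdraw from the study as a result of this AE".

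The log in the original protocol has the same fields, so the final version inherits the gap.

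**The concern.** A closed list should give every event one truthful code. This one covers events that have ended, events that are improving, deaths, and events whose status is not known. An injury that is unchanged or worse when the participant is seen is none of these. Whoever fills in the form must choose a code that misstates what they have just been told.

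What is at stake is the safety record. The trial asks people aged 60 or over to exercise more, so a lasting injury is one of the outcomes the log should show clearly. If stable or worsening events are spread over the recovering and unknown codes, a count of either code is contaminated and a count of persisting harm cannot be made from the codes.

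**Working it through.** The plan gives no figure on this point and no adverse event rates, so the check is to set the possible states of an event at a visit against the codes offered. The seven states below are a plain logical division and do not come from the protocol.

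| State of the event at the visit | Truthful code on the log |
|---|---|
| Ended, nothing left behind | 1 |
| Ended, with lasting effects | 2 |
| Not ended, improving | 3 |
| Not ended, stable | none |
| Not ended, worsening | none |
| Status not known | 4 |
| Fatal | 5 |

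Five of the seven states have a code. Of the three in which the event is known to be still present, one has a code and two do not.

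The next step is to see whether anything else in the final protocol fills the gap.

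1. **Code 2.** This is for an event that has resolved and left sequelae. An injury that has not resolved does not qualify, even if it is stable.
2. **End date.** An empty field fits an event that is improving, stable or worsening, one whose end date is unknown, and one that nobody followed up. With no rule for a blank, it cannot tell these apart.
3. **Severity and relation to the intervention.** These grade the event and its cause. Neither says whether it is still present or in which direction it is moving.
4. **Free text.** The action column allows an explanation under its last option. A note there could describe a persisting event, but it is not a coded outcome and nothing asks for it.
5. **Later screening.** Events are screened for again at the next visit, but no passage says whether an open entry is then updated. The visits are at baseline, 4 weeks, 8 weeks, and 6, 12 and 24 months. From 8 weeks to 6 months (about 26 weeks) is about 26 − 8 = 18 weeks, or roughly four months, so a wrong status entered at the 8-week visit can stand for that long.
6. **Telephone Counseling Record, Appendix B.** It notes missed goals, absences and their reasons, and special cases. It covers intervention participants during the weekly calls of the programme. It does not hold the outcome of an adverse event and is not linked to the log.

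None of these supplies the missing code.

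Two further checks bound the consequence. The rule for reporting to the Institutional Review Board turns on seriousness, unexpectedness and relation to the study. Each has its own column, so that rule does not depend on the outcome code. The Data Analysis Plan describes no analysis that uses the outcome code, so the gap enters no planned efficacy result.

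**The case against.** The strongest reply is that the gap is narrow. The log does code an unresolved event if it is improving, it has an end date, and it records severity and relatedness. Events are screened repeatedly, and a careful assessor can write a note. All of this is correct. It rules out any claim that ongoing events as a class have no code, or that every unresolved injury is lost from the record. It does not supply a truthful code for the stable or worsening event.

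A reader might also infer something stronger from the participation column: that people who stop exercising after an event will be recorded as withdrawn, lose their 8-week outcome, and so bias the primary comparison towards the intervention. The documents do not support this.

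- The column asks about leaving the study. For someone who stops exercising but stays in follow-up, the correct answer is no.
- Data Collection and Data Management and monitoring set fixed visits that do not depend on whether the participant is exercising. Under Trial Organization, a separate assessment team collects the outcomes.
- The primary analysis states: "An intention-to-treat analysis that includes all randomized participants, regardless of the number of assessments obtained, will be conducted". The missing-data section will "employ restricted maximum likelihood using all available data", with multiple imputation as a sensitivity analysis.
- The counselling record already captures missed goals, absences and the reasons for them. The call script for people who exercised less tells staff to encourage them to readjust their goals.

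It remains true that the log has no coded field for stopping the programme and that no sentence says outright that visits continue afterwards. That is missing detail. The bias would need staff to misuse the form. Expressing it as a share of the planned effect size of 0.42 would need an event rate and an outcome deficit that the documents do not give.

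**Conclusion.** The point holds for the outcome code only. The list has no valid entry for an unresolved event that is stable or worsening, nothing else in the final protocol fills the gap, and filling in the form as written produces a false or empty status for such events.

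Its size cannot be stated as a number. The affected entries are those events that are neither ended nor improving when seen, and the documents give no basis for estimating how many there will be. The severity is low: expedited reporting and the primary analysis are untouched, and the harm is confined to how well the safety record describes persisting events. The conclusion assumes that the log is used as printed, without separate completion instructions; none are shown.

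No claim is made about loss from the intention-to-treat analysis or bias in the 8-week comparison.

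**What to change.** Add one outcome code to the Adverse Event Log, for example *6 = Not recovered/ongoing*, for an event that is still present and not improving when the participant is seen. If entries have already been made, recheck those coded as recovering or unknown against the source notes. The cost is one extra code.

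Optionally, and only as a clarification of the record, add a yes/no item for stopping the intervention because of the event, separate from withdrawal from the study. This adds one column and concerns data capture only.
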